## Abstract

**Background:**

Driving under the influence (DUI) of alcohol is a major public health concern, and many individuals continue to drink and drive even after being convicted of a DUI offense. Latinos, in particular, are disproportionately likely to be arrested for a DUI, have higher rates of recidivism, and are more likely to die in alcohol-related accidents than non-Latino Whites. Latinos also experience significant disparities in accessing alcohol-related treatment.

**Methods/design:**

This study protocol paper describes a randomized trial of cognitive behavioral therapy (CBT) compared to usual care in DUI programs for individuals with a first-time offense and at-risk drinking. We will utilize a two-group randomized design where individuals enrolled in a DUI program with a first-time conviction will be randomized to CBT (n = 150) or usual care (n = 150). Participants will be assessed at baseline, immediately post-treatment, and 6-months post-treatment. Recidivism data will be collected using administrative data within 2 years post-treatment.

**Discussion:**

This project has the potential to benefit a large population of vulnerable individuals who are at risk of DUI recidivism. It also develops a new model of care by providing treatment in DUI programs to reduce disparities associated with poor treatment access.

*Trial registration* NCT02588703

## Background

Preventing recidivism among individuals convicted of driving under the influence (DUI) is an important public health objective. Individuals convicted of a DUI often continue to drive while intoxicated [1–4]. Drivers with repeated offenses are also more likely to be involved in fatal crashes. In 2010, intoxicated drivers involved in fatal crashes were four times more likely to have a prior DUI conviction than drivers in fatal crashes who were not intoxicated [5].

Addressing DUI recidivism in the Latino population is particularly important because compared to other ethnic groups, Latinos are disproportionately more likely to be arrested for a DUI, have higher rates of recidivism, and are more likely to die in alcohol-related crashes [6–10]. Although some have noted important variations in these outcomes across socioeconomic status and place of birth, the patterns of consumption among certain Latino subgroups continues to be a cause for concern [11]. For example, in a sample from Texas, Latinos were more likely than whites to report more days of heavy drinking [9, 12]. Latinos are also significantly less likely than Whites to seek specialty alcohol or drug treatment programs, and these odds worsen with alcohol use severity [13–15]. Latinos face significant structural barriers to treatment access including stigma, financial worries, difficulty finding services, and having limited or no insurance [16, 17]. Innovative treatment models that address these barriers are needed to reduce this health disparity and address rates of alcohol use disorders (AUD) in this population [18].

One reason for the high rates of recidivism among both Latinos and other populations may be because many individuals convicted of a DUI have an unrecognized and untreated AUD [19], which typical interventions provided by DUI programs may not fully address. The majority of DUI program content consists of alcohol education or information about the consequences of drinking and driving [20]. Group counselling is also provided, though the content is not standardized across the program. Rates of AUD appear to increase with multiple DUI convictions [21] and in one study, continued to be present even 15 years after a first DUI [22]. Those with multiple DUI convictions are five times more likely to have a diagnosis of AUDs than the general population [22]. While these rates are high [23], rates of AUDs are likely higher than documented because of underreporting among those with repeat offenses [24]. There is a need to examine whether providing treatment for AUD to individuals attending DUI programs could decrease recidivism.

Numerous randomized controlled trials have demonstrated that CBT is an effective treatment for alcohol abuse and dependence [25–30], yet few studies have evaluated CBT in DUI programs [31–33]. Because Latinos are less likely than Whites to access specialty alcohol use treatment, providing cognitive behavioral therapy (CBT) within a mandatory DUI program may reduce disparities in treatment access and improve alcohol-related health outcomes. It may also improve physical and mental health-related functioning [31, 34–37] and decrease future injuries and alcohol-related hospitalizations [38–40]. CBT is a counselling approach that utilizes coping skills, problem solving, and cognitive restructuring to address how individuals’ thoughts, actions/behaviors, and feelings influence each other [41]. Combined with coping skills training, CBT is one of several highly ranked evidence-based treatment programs [42, 43]. Unfortunately, while several studies suggest that CBT is acceptable and effective among Latinos, these studies have focused on CBT for depression and not drinking [44–49].

To address the dual problem of DUI recidivism and the lack of alcohol treatment utilization by Latino populations, we designed a study to evaluate the efficacy of CBT in DUI programs. We describe the study protocol of a two-group randomized trial where individuals enrolled in a DUI program with a first-time conviction will be randomized to CBT or Usual Care (UC).

### Specific aims and hypotheses

The specific aims of this project are to: (1) evaluate the efficacy of CBT on reported heavy drinking, percent days abstinent, alcohol-related self-efficacy, and intent to drink and drive; and, (2) evaluate factors associated with improved treatment outcomes and 2-year DUI recidivism by examining whether race/ethnicity, gender, acculturation, and alcohol situational norms predict treatment outcomes and DUI recidivism. We hypothesize that those randomized to CBT will have greater improvements in alcohol-related outcomes at 6-month follow-up and lower likelihood of recidivism two years later than those in UC.

## Methods/design

### Overview of study procedures

All procedures have been approved by the Institution’s Review Board. There are two phases to the study. The first phase will be focused on adapting the CBT treatment for the DUI population by eliciting feedback about each session from focus group participants. The second phase will be a randomized trial of the adapted 9-session CBT treatment compared to Usual Care. Potential participants will be screened for at-risk drinking using the AUDIT-C [four or more (if male) or three or more (if female or other)] [50], randomized to either UC or CBT, and then asked to complete self-administered assessments at baseline, immediately post-treatment (i.e., 3-months post-baseline), and 6-months post-treatment. We will also assess recidivism up to 48 months after the treatment ends using administrative data collected by the State of California. Analyses will be conducted to compare overall group efficacy between CBT and UC. We will also analyze predictors of treatment response and recidivism by examining whether race/ethnicity, gender, acculturation, and alcohol situational norms predict treatment outcomes and DUI recidivism.

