### Phase 2 procedures

The purpose of Phase 2 is to determine the efficacy of a 9-session CBT group treatment for AUD compared to UC among individuals who are court-ordered to attend a 3-month DUI program for a first-time conviction. We will also examine predictors of CBT efficacy to further understand the characteristics of participants who benefit most from treatment.

Participants (N = 300) will be recruited at intake (see Fig. 1). Upon enrolling in the DUI program, program staff will ask clients if research staff can contact them about a research study. Interested clients will complete a consent-to-contact form. After DUI program staff has completed their procedures, on-site research staff will screen, obtain consents, and randomize potential clients. For rare instances when staff is unavailable, DUI staff will fax consent-to-contact forms to a secure fax machine and research staff will screen and gain consent from the client by phone. Staff will screen for at-risk drinking using the AUDIT-C [four or more (if male) or three or more (if female or other)] [50]. Participants will be asked to complete a baseline survey, post-treatment survey at DUI program completion (i.e., 3-months post-baseline), and a follow-up survey 6 months after program completion. Participants will receive a $25 gift card for the baseline survey, $25 for the post-survey, and $50 for the 6-month follow-up. All participants will be followed, regardless of whether they complete UC or CBT, and we will conduct intent to treat analyses.

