### Phase 2 analysis plan

We will use an intent-to-treat (ITT) approach, in which all persons who complete baseline will be assessed. Thus, the overall efficacy of the treatment will include the effect of attrition and non-compliance. DUI programs will not use special procedures to keep clients in our experimental treatment. Analyses will use the standard ITT approach to examine the effect of offering the CBT to all participants. Our ITT approach will analyze participants as belonging to the group they were randomized to, regardless of their compliance or attrition, because excluding clients that do not attend the CBT sessions would be likely to bias our results in favor of the CBT [88].

Our primary analysis will be to examine differences in the primary outcome (rates of heavy drinking and percent days abstinent) at both follow-ups controlling for baseline and other characteristics (age, gender, ethnicity; see Table 2). Similar analyses will be conducted for the secondary (self-efficacy, intent to drink and drive) outcomes. The rolling group design violates the independence assumption [89, 90]. Analyses will adjust for the rolling group design using a multiple membership model [91].

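### As written, randomization comes before the self-reported baseline survey while the intent-to-treat set is limited to baseline completers; the order and the set definition should both be changed

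*Protocol article*

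**What the plan says.** **Order of steps.** Under Overview of study procedures, potential participants are screened with the AUDIT-C, "randomized to either UC or CBT, and then asked to complete self-administered assessments at baseline" and at the two later time points. Under Phase 2 procedures, "on-site research staff will screen, obtain consents, and randomize potential clients". Some sentences later, "Participants will be asked to complete a baseline survey". That section does not say outright which comes first. Nothing in the text puts the baseline survey before randomization.

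**Analysis set.** The Phase 2 analysis plan opens: "We will use an intent-to-treat (ITT) approach, in which all persons who complete baseline will be assessed". The same paragraph calls this the standard approach and says it will "analyze participants as belonging to the group they were randomized to, regardless of their compliance or attrition". Phase 2 procedures add: "All participants will be followed, regardless of whether they complete UC or CBT".

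**Use of baseline.** The primary analysis compares heavy drinking and percent days abstinent "at both follow-ups controlling for baseline and other characteristics". Table 2 shows that drinking is measured with the Daily Drinking Questionnaire at baseline and at both follow-ups.

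**The concern.** Two consequences follow if the overview and the analysis plan are both taken at their word.

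1. Completing the baseline survey becomes an event after randomization, and membership of the intent-to-treat set depends on it. Someone who is allocated and then does not return the survey is lost from the comparison. The plan itself argues that leaving out people who do not attend CBT would bias the result; the same reasoning applies to people lost at the first survey.
2. The main adjustment covariate is a self-report collected after allocation. If participants know their arm by then, and this changes what they report, adjusting for that report moves the estimated treatment effect.

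Both bear on the primary comparison. The second cannot be fully repaired in the analysis, because a baseline reported after the arm is known cannot be measured again.

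**Working it through.** **Reproducing the plan's figure.** 300 people allocated 1:1 to two conditions gives 300 / 2 = 150 per arm, as stated under Flow rates. The article gives no standard deviation, correlation or effect size, so there is no power calculation to reproduce.

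**Reading the sections together.**

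| Section | Order or set | Explicit? |
|---|---|---|
| Overview of study procedures | Randomize, then baseline | Yes |
| Phase 2 procedures | Screen, consent, randomize; survey mentioned later | Implied by sentence order only |
| Phase 2 analysis plan, first statement | Set = baseline completers | Yes |
| Phase 2 analysis plan, later statement | As randomized, regardless of attrition | Yes |

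Under the order in the overview, the last two rows differ for anyone randomized who has no baseline survey. If the survey came first, the two rows would describe the same people.

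**Number excluded.** Let *m* be the share randomized without a baseline survey. The article does not give *m*, so 0 to 15% is assumed. The number left is 300 × (1 − *m*). The number with 6-month data at the stated 85% retention is that × 0.85.

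| *m* | Excluded | Left | With 6-month data |
|---|---|---|---|
| 0% | 0 | 300 | 255 |
| 5% | 15 | 285 | 242 |
| 10% | 30 | 270 | 230 |
| 15% | 45 | 255 | 217 |

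**Selection effect.** Suppose excluded people differ from included people by *D* SD on the outcome, in the same direction in both arms. The mean of those included shifts by −*m* × *D* in each arm, so the between-arm shift has size (*m* in CBT − *m* in UC) × *D*. All inputs here are assumed.

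- 5% in both arms, any *D*: zero.
- 10% v 5%, *D* = 0.5: 0.05 × 0.5 = 0.025 SD.
- 15% v 5%, *D* = 1: 0.10 × 1 = 0.10 SD.

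**Covariate effect.** With equal SDs at baseline and follow-up and correlation *r*, the covariate-adjusted effect is the follow-up difference minus *r* times the baseline difference. A pure reporting shift of *d* SD at baseline in one arm, with follow-up reports unaffected, therefore moves the estimate by *r* × *d* in the opposite direction. Assume *r* = 0.6.

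- *d* = 0.1: 0.6 × 0.1 = 0.06 SD.
- *d* = 0.2: 0.6 × 0.2 = 0.12 SD.

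The adjusted standard error is √(2/*n*) × √(1 − 0.36), with *n* per arm.

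- *n* = 150: 0.1155 × 0.8 = 0.092 SD, a ratio of 0.65 to 1.3.
- *n* = 150 × 0.85 = 127.5: 0.1252 × 0.8 = 0.100 SD, a ratio of 0.6 to 1.2.

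The second line fits the 6-month outcome. Clustering from the rolling groups, which the plan acknowledges, would enlarge the standard error and lower the ratio further.

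**The case against.** The strongest reply is that the order rests on one phrase in a condensed overview. Phase 2 procedures do not confirm it independently: the sentence on AUDIT-C screening also follows the one on randomization there, although screening must come first, so sentence order proves little. Figure 1, the data collection flow, was not available for this review and may show another order. If the survey is in fact done first, the set of baseline completers is everyone randomized and the analysis paragraph is consistent. This stands as a limit on certainty, but the phrase is explicit and nothing in the text contradicts it. If practice is baseline first, the overview is wrong and needs the same correction.

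Three stronger readings are tempting and are not supported.

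- *Randomized people will be excluded.* No rate is given. Recruitment is at intake, usually with staff on site, and the survey carries a $25 gift card. The number could be zero, and equal loss with equal selection in both arms shifts nothing.
- *The baseline covariate is biased.* The article describes no masking, and participants must eventually learn which groups they attend. It does not say that they know their arm when they answer the survey. The AUDIT-C screen is taken before randomization, so eligibility is unaffected.
- *The recidivism analysis wrongly drops these people.* The baseline-completer wording belongs to the Phase 2 plan. The Phase 3 plan for recidivism has no such restriction. Its predictors include acculturation and situational norms, which come from the baseline survey, so a person without that survey would lack them. The article does not state that motor vehicle records can be obtained for everyone randomized.

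**Conclusion.** The point holds as a defect in what is written. The overview places allocation before a self-administered baseline, the analysis plan limits its intent-to-treat set to those who complete that baseline, and the primary model adjusts for it. The set definition then conflicts with the commitment, in the same paragraph, to analyze as randomized regardless of attrition.

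The consequence is a risk, not a demonstrated bias. The shift of 0.06 to 0.12 SD needs the arm to be disclosed before the survey, a resulting reporting shift of 0.1 to 0.2 SD and a correlation of 0.6; the article gives none of these. The selection shift of 0.025 to 0.10 SD needs different completion rates by arm and excluded people who differ from the rest. Either could be nil. The change is still worth making, because it removes both risks at little cost.

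**What to change.** 1. **Overview of study procedures and Phase 2 procedures:** reword so that screening, consent and the baseline survey are all complete before the participant's allocation is generated or disclosed, and check that Figure 1 shows this order. If the sequence is drawn up in advance, as the article says, the requirement is that the next assignment is not opened until the survey is in.
2. **Phase 2 analysis plan:** define the intent-to-treat set as all randomized participants, analyzed in the arm assigned. Handle any missing baseline value without using arm.
3. **Recidivism:** any comparison by arm should include all randomized participants whose records can be obtained.

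The cost is wording and visit order. Randomization waits for the survey, which may slow the few phone enrolments, and people who refuse the survey are not randomized.

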### Study setting

We will draw upon an existing collaboration with the Los Angeles County Substance Abuse Prevention and Control (LAC-SAPC) and three private DUI programs under LAC-SAPC’s regulatory authority. In Los Angeles County, when an adult is arrested for DUI for the first time, in addition to having a suspended driver’s license and other sanctions, the individual must also attend a 3-month DUI program that meets California’s Title 9 requirements [51].

The three participating DUI programs provide English and Spanish-speaking services to diverse clientele. Individuals enrolled in a 3-month DUI program attend a minimum of 12 h of alcohol and drug-related educational classes, 18 h of group counselling, and three individual assessment interviews [51]. Educational classes focus on the effects of alcohol and other drugs; nature of addiction to alcohol and drugs; impairment of driving abilities, skills, and judgment caused by consumption of alcohol or drugs; alternatives to the abuse of alcohol and drugs; and the effects of alcohol or drug use on the individual, family, and society. Group counselling focuses on encouraging clients to share ideas, examine their personal attitudes and behavior, and provide support for any positive changes. Of note, no specific guidance on the content or style of the counselling groups is given by State law so it is unknown whether these groups provide evidence-based treatment. Face-to-face individual interviews occur at the beginning, midpoint, and end of the program to monitor fee payment, attendance, barriers to program completion, and assessment of additional services needed [52].

### Participants

Only English-speaking clients will be recruited based on our previous work showing small proportions of Spanish-only speaking clients in our participating programs [19, 53]. Participants will be English-speaking individuals 21 and older who are convicted of a first-time DUI offense and enter one of the three participating 3-month DUI programs in LA County. We will recruit individuals with first-time offenses rather than individuals with a repeat offense to control for treatment dose, as individuals with repeat offenses attend longer programs. Participants will be screened for at-risk drinking using the AUDIT-C [50].

We plan to recruit all eligible individuals with at-risk drinking who have been convicted of a first-time DUI regardless of ethnicity because we do not want to exclude clients from the possibility of treatment while in the DUI program. We expect that our population for sampling will be 65 % male; 50 % Hispanic/Latino, and 10 % African American.

### Description of CBT treatment

The proposed CBT treatment [32] has been shown to be effective in reducing drinking and improving coping skills across several randomized trials [32, 54–57], and has been adapted as an individualized treatment for AUDs in Project MATCH [58]. The treatment is designed to be delivered in a group format for nine 90-min sessions with two optional sessions on nonverbal communication and assertiveness [32].

To meet Title 9 requirements and to keep treatment dosage the same as UC, the current study will deliver nine sessions once per week, each lasting 2-h (see Table 1). The goals of the CBT treatment will be to reduce drinking and related consequences including drinking and driving.

**Table 1 Tab1:** Proposed CBT sessions

Session	Session topic
1	Making informed choices about drinking
2	Managing urges to drink
3	Connecting situations, thoughts, and feelings
4	Managing negative thinking
5	Receiving criticism about drinking
6	Seemingly irrelevant decisions
7	Communication skills
8	Developing social support networks
9	Increasing pleasant activities

*Session 1* Counsellors will focus on educational information about alcohol and alcohol’s effects on decision making in order to assist participants in their ability to make informed decisions and how much to drink [59].*Session 2* Participants will learn to identify and cope with different high-risk situations that can increase the likelihood of drinking and driving [32, 60].*Session 3* Counsellors will help participants understand the connection between thoughts, feelings, and behavior as it relates to drinking in particular [60]. Participants will be introduced to how their thoughts and feelings are directly connected with their behaviors.*Session 4* Participants will learn helpful strategies to identify and manage their negative thinking using cognitive restructuring techniques. Participants will complete a cognitive restructuring chart called “Catch it, Check it, Change it” [60] that helps participants identify and change harmful thoughts that lead to drinking and driving.*Session 5* Participants will be introduced to skills that will help them cope with criticism from others about their drinking [32]. Participants will learn different types of criticism and strategies to cope with each (e.g., react less defensively, find something to agree with, work out a compromise).*Session 6* Participants will learn how to identify seemingly irrelevant decisions that lead to drinking and/or drinking and driving [32]. Participants will learn that these decisions are ordinary choices we make every day that eventually lead to drinking and/or drinking and driving. Participants will complete a chaining exercise examining the decisions that lead up to their last drinking and/or drinking and driving episode.*Session 7* Participants will learn useful skills that will help them improve their communication, and thus increase their friendships and supportive network. They will learn the differences between passive, aggressive, passive-aggressive, as well as assertive communication, and will role-play asking assertive requests.*Sessions 8 and 9* Counsellors will discuss helpful strategies to increase their support network and enjoyable non-drinking activities that can be accomplished either alone or with others.

In each session, the rationale for the session will first be described as it relates to drinking behavior and preventing future DUI, and then the content of the module or “skill guidelines” will be reviewed. The counsellor and participants then practice skills using role plays and group exercises. Because each session is self-contained and includes a review of the rationale and skill guidelines, the group can have “rolling admission,” in which members can join at any session in the treatment. Rolling CBT groups are common and more sustainable in community settings [44–49], which makes the proposed CBT groups more comparable to UC.

